#### Primary Analysis for the Primary Outcome

The primary outcome will be analyzed using a linear regression model adjusted for age and baseline DD to assess the effect of the MSC-T intervention on DD at the 3-month time point. We will adjust for age to account for the variability in the developmental stage of each participant, which may impact their response to the mindful self-compassion (MSC) program. We will also account for baseline levels of DD as we are assessing the change in DD from baseline to 3 months.

#### Secondary Bayesian Analysis for the Primary Outcome

Although our trial is powered to detect a moderate effect size of 12 points on the PAID-T, we acknowledge that a smaller effect size is still clinically meaningful. Bayesian methods focus on providing plausible values for the intervention effect that are compatible with both the observed data and previous knowledge and beliefs. Bayesian analysis enables the use of both noninformative priors that minimize the influence of priors on the statistical inference and informative priors that are guided by existing evidence or a range of collective expertise from investigators regarding the belief or skepticism of the intervention’s efficacy. Thus, a secondary Bayesian analysis will complement our frequentist analysis in the interpretation of our randomized trial results [57]. Following existing Bayesian analysis reporting guidelines [58], we will conduct a prespecified Bayesian linear regression analysis to examine the probability that the MSC-T intervention reduces DD in a clinically meaningful way compared with the control group based on the trial results.

The main objective of the Bayesian analysis is to determine the posterior probability (also known as an updated probabilistic belief) that the MSC-T intervention (1) affects PAID-T scores and (2) reduces DD by between-group differences on the PAID-T of 7-15 points (eg, effect size of 0.27-0.5), given the prior distributions of the treatment effect and the observed data from the trial. We considered an effect size of 0.27 as the minimum threshold for potential clinical relevance, given the strong relationship between DD and clinical outcomes [3], and based on the expert opinions of our team of experienced diabetologists.

To reflect our uncertainty around the effect of the MSC-T intervention, we will use a range of priors representing varying degrees of enthusiasm and skepticism (Multimedia Appendix 3). In the Bayesian regression analysis, noninformative priors will be used for nuisance parameters, including the regression intercept terms and the parameters that do not quantify the MSC intervention effectiveness. The convergence of Bayesian estimation will be examined using trace plots and the R^ convergence index with a cut-off of 1.01 [59]. With the trial data, we will estimate the 95% credible intervals using Markov chain Monte Carlo (MCMC) sampling techniques with at least 2 parallel chains [58] and report the estimated posterior probabilities for different magnitudes of treatment effects as specified in Multimedia Appendix 3. The analysis will be conducted in R statistical software [24], and Bayesian analysis will be performed using Stan MCMC (Stan Development Team) [60].

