### Randomization Procedures

We will use the randomization module in REDCap [21,22] to allocate participants to their group. The randomization table will be created by a study team member who is not directly involved in patient recruitment or data collection using R (R Core Team) [24]. The trial coordinator will generate the allocation for each participant following obtaining informed consent and completion of the baseline assessments (ie, there will be hidden allocation).

Participants will be randomly allocated to either the MSC-T intervention group or the waitlist control group using a 1:1 ratio block randomization. We will stratify each block by age group (12-14 years [early adolescence] or 15-17 years [middle adolescence]). The cohort will be divided by these age groups to deliver the intervention with the goal of fostering a developmentally appropriate and open environment. Stratification by age group is therefore necessary to ensure an equal age distribution between the treatment groups, since the developmental age of a participant could impact their response to the intervention [25]. We will also randomly vary the block size, with blocks of either 6 or 8, to prevent prediction of group allocation as participants are accrued [26].

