### Statistical Plan

#### Sample Size

Our target sample size is 70 participants per group (140 participants total). This sample size achieves 80% power to detect group differences of 12 points or more [53] using a 2-sided significance level of 5% [26]. In this calculation, we assumed a mean PAID-T score of 73 in the waitlist control group with a SD of 26 [54]. A 30% attrition rate, based on previous relevant trials [55], was also considered.

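### The upper end of the Bayesian target range does not match the plan's SD (15 points is 0.58, not 0.5), and the targets should be stated as one-sided exceedance probabilities

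*Protocol article*

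**What the plan says.** The section Secondary Bayesian Analysis for the Primary Outcome names two posterior probabilities as the main objective of that analysis. The first is "the posterior probability (also known as an updated probabilistic belief) that the MSC-T intervention (1) affects PAID-T scores". The second is that it "reduces DD by between-group differences on the PAID-T of 7-15 points (eg, effect size of 0.27-0.5"). The same section takes 0.27 as the smallest effect size of potential clinical relevance and gives no upper limit. Its preceding paragraph states a directional aim: the probability of a clinically meaningful fall in distress.

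The scale comes from the Sample Size section: "we assumed a mean PAID-T score of 73 in the waitlist control group with a SD of 26". No other PAID-T standard deviation appears in the article.

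The section goes on to say that a range of priors will be used, that 95% credible intervals will be estimated, and that posterior probabilities for several sizes of effect will be reported as listed in Multimedia Appendix 3. That appendix is not shown.

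**The concern.** The range is given on two scales that should be translations of each other, and they agree only at the lower end. A reader cannot tell whether the upper value is 13 or 15 points.

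A reduction of 7 to 15 points, read as written, is also an interval with a top. An effect above 15 points falls outside it, so a large benefit lowers the reported probability. That does not fit an analysis whose stated relevance criterion is a minimum.

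The article offers this analysis as the way to judge effects smaller than the 12 points used for power, so these probabilities are likely to be read as evidence on clinical relevance. If interval or threshold, and 13 or 15 points, stay open in the text, the choice could be made after the results are known.

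**Working it through.** **Inputs from the article.** SD 26 (Sample Size); target range 7-15 points and 0.27-0.5 (Bayesian section); "Our target sample size is 70 participants per group (140 participants total"); "A 30% attrition rate, based on previous relevant trials", which leaves 70 × 0.70 = 49 per arm.

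**Assumptions.** A flat prior, a normal posterior and a baseline-to-3-month correlation r. The article gives no r, so two cases are shown: 49 per arm with r = 0, and 70 per arm with r = 0.5.

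**Step 1: the two scales.** Effect size = points / SD.
- Lower end: 7/26 = 0.269. This reproduces the stated 0.27.
- Upper end: 15/26 = 0.577. This does not reproduce 0.5, and it rounds to 0.58 or 0.6.
- In reverse: 0.5 × 26 = 13 points.
- Implied SDs: 7/0.27 = 25.9 and 15/0.5 = 30. An SD of 30 would fit the top but not the bottom, since 7/30 = 0.23. No single SD fits both ends.

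**Step 2: interval against threshold.** The standard error is SE = 26 × √(1 − r²) × √(2/n).
- n = 49, r = 0: 26 × √(2/49) = 5.25.
- n = 70, r = 0.5: 26 × √0.75 × √(2/70) = 3.81.

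For an observed reduction d, the interval probability is Φ((15 − d)/SE) − Φ((7 − d)/SE). The threshold probability is 1 − Φ((7 − d)/SE). For example, at d = 15 and SE 5.25 the interval gives Φ(0) − Φ(−1.52) = 0.500 − 0.064 = 0.436, and the threshold gives 1 − 0.064 = 0.936.

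| Observed reduction | 7-15, SE 5.25 | ≥7, SE 5.25 | 7-15, SE 3.81 | ≥7, SE 3.81 |
|---|---|---|---|---|
| 11 | 0.554 | 0.777 | 0.707 | 0.853 |
| 12 | 0.545 | 0.829 | 0.690 | 0.906 |
| 15 | 0.436 | 0.936 | 0.482 | 0.982 |
| 20 | 0.164 | 0.993 | 0.094 | 1.000 |
| 25 | 0.028 | 1.000 | 0.004 | 1.000 |

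The interval probability peaks at its midpoint, (7 + 15)/2 = 11, whatever the SE. The threshold probability rises throughout.

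**Step 3: the first target.** It names no direction. Under a prior with no point mass at zero, the posterior probability of a non-zero effect is 1 whatever the data, so the literal wording carries no information. The probability of a reduction greater than zero does.

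**The case against.** The upper end carries little weight. Only the lower end is tied to clinical relevance, and it is right on both scales. No success rule, sample size or primary test uses 15 points, and the model works on PAID-T points, so the standardized figure is a gloss. All of that stands. It limits the consequence but does not make the two scales agree.

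A reader might infer that the plan will report stronger results as less likely to be meaningful. The article does not establish that. Reporting several sizes of effect from Multimedia Appendix 3, together with a minimum relevant effect, fits a series of cut-offs running from 7 to 15 points. Such a series would not have this defect. The planned credible intervals would also make a large benefit visible. The interval problem therefore holds only if the range is computed as a closed band.

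A reader might also infer that the first target is empty by design. The directional aim stated just before it, and the hypothesis of lower distress, make the probability of any reduction the likely intent. The priors are in the appendix and cannot be checked. This is loose wording.

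Finally, the figures in the table rest on a flat prior and assumed correlations, while the plan includes skeptical and enthusiastic priors. The sizes would change with the prior and r. The peak at 11 points holds for any symmetric, single-peaked posterior, with 11 then being the posterior mean.

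**Conclusion.** The mismatch is certain: on the plan's SD of 26 the range is either 7-15 points = 0.27-0.58 or 7-13 points = 0.27-0.5. The article does not show which was meant.

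The interval problem is conditional on a literal reading. On that reading it is large: at an observed 20-point reduction the band gives 0.16 (49 per arm, r = 0) or 0.09 (70 per arm, r = 0.5), where the probability of at least 7 points is 0.99 or higher. Whether the appendix already avoids this cannot be judged from what is shown.

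The wording of the first target needs only clarification. All of this concerns a secondary analysis; the primary regression test is unchanged.

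**What to change.** Correct the pair to 7-15 points = 0.27-0.58, or to 7-13 points = 0.27-0.5, whichever was meant, and name the SD used.

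State the targets as one-sided exceedance probabilities under each prior: P(reduction > 0) in place of the undirected first target, and P(reduction ≥ 7 points) for the minimum relevant effect. Add any higher thresholds wanted, up to the corrected upper value. Check that Multimedia Appendix 3 gives the same definitions; if it already does, the main text only has to match it.

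The cost is wording. No data collection, sample size or model changes. The correction should be on record before results by arm are seen.

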#### Analyses for Secondary Outcomes

Linear regression models and generalized linear regression models (for binary or categorical secondary outcomes), adjusting the same covariates as the primary analysis, will be used to assess the effect of the MSC-T intervention on our secondary outcomes of (1) depression, anxiety, disordered eating symptoms, and suicidal ideation at 3 months; and (2) DD, depression, anxiety, disordered eating symptoms, and suicidal ideation at 12 months.

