#### Analyses for Exploratory Outcomes

To explore the effect of the MSC-T program on DD over time, we will use the 3-, 6-, and 12-month data to fit a linear mixed effects model, adjusted for time, age, baseline DD, an interaction term for time and group, and a random intercept (to account for repeated measures).

Exploratory outcome HbA_1c_ at 12 months will be modeled in a linear regression adjusted for age and baseline HbA_1c_. Linear mixed effects models, adjusted for age, baseline time in range, and a random intercept, will be used to assess the effect of the MSC-T intervention on the repeated measure time in range. Interaction terms between group and gender will be included in a separate model to investigate how the MSC-T intervention differs based on self-reported gender (collapsed to male, female, and gender-diverse for the purposes of analysis) at the primary end point.

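### The models for anxiety, depression, disordered eating and suicidal ideation adjust for baseline diabetes distress but not for the outcome's own baseline, which costs precision and only partly corrects chance imbalance

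*Protocol article*

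**What the plan says.** Under Primary Analysis for the Primary Outcome, the protocol article specifies a "linear regression model adjusted for age and baseline DD". It gives this reason for the second covariate: "We will also account for baseline levels of DD as we are assessing the change in DD from baseline to 3 months". Baseline DD is there because it is the baseline of the outcome being analysed.

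Under Analyses for Secondary Outcomes, the covariate set is carried over unchanged: "adjusting the same covariates as the primary analysis, will be used to assess the effect of the MSC-T intervention on our secondary outcomes". The outcomes listed are "depression, anxiety, disordered eating symptoms, and suicidal ideation at 3 months" and "DD, depression, anxiety, disordered eating symptoms, and suicidal ideation at 12 months". That makes nine comparisons, and in eight of them the outcome is not DD.

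Under Analyses for Exploratory Outcomes, the rule differs. HbA1c is "modeled in a linear regression adjusted for age and baseline HbA_1c", and the time-in-range model is "adjusted for age, baseline time in range, and a random intercept". Each uses its own baseline.

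Table 3 (schedule of activities) shows the PHQ-9, GAD-7 and DEPS-R completed at baseline. Under Randomization Procedures, the only stratification factor is age group.

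**The concern.** The reason given for baseline DD applies only when DD is the outcome. Carried over to the other outcomes, it puts in the baseline of a different scale and leaves out the covariate that is usually the strongest predictor of the follow-up score. No reason is given for treating these outcomes differently from HbA1c and time in range.

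Two things are at stake. The first is precision: a less predictive covariate leaves more residual variance and gives wider intervals for the continuous scores. The second is conditional imbalance: nothing in the design balances baseline anxiety, depression, disordered eating or ideation between arms. If the arms differ on one of these by chance, part of that difference stays in the estimated effect.

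**Working it through.** **Inputs from the article.** 70 per group and 30% attrition (Sample Size), so 70 × 0.7 = 49 completers per arm. The article states no correlations, and no precision or power for secondary outcomes, so there is no figure of its own to reproduce on this point.

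**Assumptions (not in the article).** ρ is the correlation of the follow-up score with its own baseline, 0.5 to 0.7. c is its correlation with baseline DD, 0.3 to 0.5, always below ρ. g is the correlation between the two baselines, 0.5 to 0.6. All are taken as holding after adjustment for age. GAD-7, PHQ-9 and DEPS-R are taken to be analysed as continuous scores.

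**Step 1: count the comparisons.** Four at 3 months plus five at 12 months is nine. DD at 12 months already has its own baseline, which leaves eight. Two of these are binary suicidal ideation, and six are continuous (three scales at two time points).

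**Step 2: residual variance, continuous outcomes.** With the total variance set to 1, the residual variance is 1 − c² after adjustment for baseline DD and 1 − ρ² after adjustment for the own baseline.

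| ρ | c | (1 − ρ²)/(1 − c²) | Reduction with own baseline |
|---|---|---|---|
| 0.5 | 0.4 | 0.75/0.84 = 0.89 | 11% |
| 0.5 | 0.3 | 0.75/0.91 = 0.82 | 18% |
| 0.6 | 0.5 | 0.64/0.75 = 0.85 | 15% |
| 0.6 | 0.4 | 0.64/0.84 = 0.76 | 24% |
| 0.6 | 0.3 | 0.64/0.91 = 0.70 | 30% |
| 0.7 | 0.5 | 0.51/0.75 = 0.68 | 32% |
| 0.7 | 0.4 | 0.51/0.84 = 0.61 | 39% |
| 0.7 | 0.3 | 0.51/0.91 = 0.56 | 44% |

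The standard error under DD adjustment is larger by the factor √[(1 − c²)/(1 − ρ²)]. This runs from √1.12 = 1.06 to √1.78 = 1.34, and is √1.31 = 1.15 in the central case (ρ = 0.6, c = 0.4).

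**Step 3: illustrative power.** Take an effect of 0.5 SD with 49 per arm, two-sided 5%, and power = Φ(0.5/[√v × √(2/49)] − 1.96), where v is the residual variance and √(2/49) = 0.202.
- Own baseline, v = 0.64: 0.5/(0.80 × 0.202) = 3.09, so power is 87%.
- Baseline DD, v = 0.84: 0.5/(0.917 × 0.202) = 2.70, so power is 77%.

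Across the grid, power is 82% to 93% with the own baseline and 74% to 82% with baseline DD.

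**Step 4: chance imbalance.** The difference in a baseline mean between arms has a standard deviation of √(2/70) = 0.17 SD units at 70 per arm and 0.20 at 49. Suppose the own baseline differs by 0.2 SD while baseline DD is balanced. DD adjustment then leaves 0.2 × (ρ − cg)/(1 − g²) in the estimate. The smallest value is 0.2 × (0.5 − 0.20)/0.75 = 0.08 SD (c = 0.4, g = 0.5). The largest is 0.2 × (0.7 − 0.18)/0.64 = 0.16 SD (c = 0.3, g = 0.6).

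If baseline DD is instead out of balance to the degree its correlation predicts, 0.2 × (ρ − cg) remains. In the central case with g = 0.5 that is 0.2 × (0.6 − 0.2) = 0.08 SD, against 0.2 × 0.6 = 0.12 SD with no baseline adjustment. Baseline DD therefore removes part of the imbalance, but not all of it.

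**Step 5: suicidal ideation.** This outcome is binary (PHQ-9 item 9 above 0) and goes into a generalised linear model whose link is not named. The ratios in Step 2 do not carry over. With a logit link, adding a strong predictor typically raises the standard error of the log odds ratio and moves the conditional estimate away from zero, while power improves.

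**The case against.** The strongest reply is that the wording is shorthand. Since baseline DD enters the primary model as the outcome's own baseline, and the exploratory models use own baselines, the authors may have meant age plus the baseline of each outcome. That is possible, and a journal article is condensed. But the article does not leave the covariates open. It states a set, and where it intends an own baseline it names it. If the shorthand was intended, the sentence still needs correcting, because an analyst who follows it literally would fit the other model.

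A reader might also infer more than the article supports:
- **That the secondary estimates are biased, or chance imbalance is wholly uncorrected.** Randomisation keeps the estimates unbiased on average, and baseline DD probably correlates with the other scores, so it takes out some imbalance.
- **That all eight intervals are wider than they need be.** The variance argument covers the six continuous comparisons, not the two on suicidal ideation.
- **That a known share of the sample is being thrown away.** The size rests entirely on assumed correlations. At 0.5 versus 0.4 the reduction is about 11%, and at 0.45 versus 0.40 it is about 5% (0.7975/0.84 = 0.95). Correlation with baseline usually weakens over time, so the gain may be smaller at 12 months.
- **That baseline DD must come out.** Nothing supports requiring its removal.

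The primary analysis, DD at 12 months and the exploratory models are not affected.

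**Conclusion.** The point holds on the text as a correction to secondary analyses. Eight of the nine secondary comparisons are set to use the baseline of another scale, against the plan's own practice for DD, HbA1c and time in range and although the right covariates are collected. For the six continuous comparisons the cost is lost precision: residual variance would be about 11% to 44% lower with the own baseline, over the assumed correlations. Chance imbalance in the own baseline is only partly corrected. For suicidal ideation the gain would be in power and in handling imbalance, and is not quantified here. The direction of the precision argument requires only that the own baseline predicts its follow-up score better than baseline DD does; the size cannot be fixed from the article.

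**What to change.** Replace the reference to the primary covariates with a statement that each secondary outcome is adjusted for age and for the baseline value of that same outcome. Baseline DD may be kept in addition, and for DD at 12 months it is already the own baseline. For suicidal ideation, use baseline PHQ-9 item 9 above 0. Because the trial excludes acute suicidality at enrolment and the article gives no ideation rate, positive counts may be sparse, so name a fallback such as penalised regression.

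Date the change and make it before unblinding. The article reports follow-up as still running and says the statistician for the primary analysis is blinded to allocation. The cost is one sentence in the plan and one further line for the sparse-data fallback; no new data are needed.

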#### Analyses for Exploratory Outcomes

To explore the effect of the MSC-T program on DD over time, we will use the 3-, 6-, and 12-month data to fit a linear mixed effects model, adjusted for time, age, baseline DD, an interaction term for time and group, and a random intercept (to account for repeated measures).

Exploratory outcome HbA_1c_ at 12 months will be modeled in a linear regression adjusted for age and baseline HbA_1c_. Linear mixed effects models, adjusted for age, baseline time in range, and a random intercept, will be used to assess the effect of the MSC-T intervention on the repeated measure time in range. Interaction terms between group and gender will be included in a separate model to investigate how the MSC-T intervention differs based on self-reported gender (collapsed to male, female, and gender-diverse for the purposes of analysis) at the primary end point.

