### Objectives

Our primary objective is to compare DD at 3 months among youth with T1D who participated in the MSC-T intervention to those in a waitlist control group. Our secondary objectives are to (1) compare anxiety, depression, diabetes-related disordered eating, and suicidal ideation at 3 months among youth with T1D who participated in the MSC-T intervention with those in the waitlist control group; and (2) compare DD, anxiety, depression, diabetes-related disordered eating, and suicidal ideation at 12 months among youth with T1D who participated in the MSC-T intervention with those in the waitlist control group. Finally, our exploratory objectives are to (1) explore if the effect of the MSC-T intervention changes over time throughout the 12-month follow-up period, (2) compare glycemic control (HbA_1c_ and time in range) among adolescents with T1D who participated in the MSC-T intervention to those in the waitlist control group, and (3) explore if the effect of the web-based MSC-T intervention on DD differs based on self-reported gender.

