#### Intervention Group

The MSC-T intervention (Textbox 2) teaches the participants to be open to, rather than disconnected from, their own suffering and treat themselves with the same care they would show to a friend [10]. The program consists of 8 weekly interactive sessions, each lasting 1.5 hours (a total of 12 hours). The program will be led by our collaborators (KB and AL), who are trained, experienced MSC-T instructors. Each session will begin with a brief mindful art activity, which provides a transition to the class. Classes include developmentally appropriate hands-on exercises, videos, games, mindful movement, music meditation, and between-class practice assignments to solidify practices. The session content and structure were reviewed by our people with lived experience collaborators (SH and OI).

MSC-T program fidelity will be determined by (1) assessing the change in self-compassion between baseline and 8 weeks and (2) assessing if the required topics for each MSC-T session were covered and activities performed. Self-compassion will be assessed using the Self-Compassion Scale for Youth, a psychometrically valid and reliable measure of self-compassion for adolescents [23]. To ensure the respective topics are appropriately covered in the MSC-T sessions, a member of the study team will complete a fidelity assessment during each session.

Participants’ satisfaction and acceptability of the intervention will be evaluated using an intervention satisfaction survey, similar to what has been previously used to determine satisfaction with the web-based MSC-T program [18].

Program summary (sessions and topics) for mindful self-compassion for teens (MSC-T) intervention.

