Symptoms of diabetes-related disordered eating will be measured using the Diabetes Eating Problem Survey-Revised (DEPS-R) version [42], a diabetes-specific measure of disordered eating symptoms that is valid for use in adolescents with T1D [42]. The DEPS-R is scored from 0-80, with higher scores indicating more disordered eating behaviors, and a score of ≥20 is suggestive of disordered eating behaviors [42]. The use of a diabetes-specific tool to measure disordered eating is important, as generic measures may overestimate the prevalence of disordered eating symptoms given that diabetes management involves an emphasis on food intake and carbohydrate counting and that insulin restriction is not captured in generic measures [43].

Suicidal ideation will be assessed using 1 question on the PHQ-9, which asks the respondent if they have had thoughts that they would be better off dead or of hurting themselves in the previous 2 weeks. This question is scored on a scale from 0 (not at all) to 3 (nearly every day). In line with previous use of the PHQ-9 [44], we will consider any score of >0 to be indicative that suicidal ideation is present.

Our exploratory outcomes are the effects of time, HbA_1c_, time in range, and effect of gender. We will assess whether the effect of the MSC-T intervention on DD changes over time by exploring the interaction of time (ie, study time point) with DD. We will assess both HbA_1c_ and time in range, as not all our clinic patients wear a continuous glucose monitor (CGM), which is necessary to calculate time in range (>70% of our clinic patients wear a CGM).

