### Trial Management

To foster an environment where the participants feel comfortable, the web-based MSC-T intervention will be conducted with groups of 12-18 participants of the same age group [18]. To ensure that there is no exclusion of youth based on socioeconomic status or access to technology, participants who do not have a computer, laptop, tablet, or webcam to attend the web-based sessions will be loaned a study tablet, and mobile internet devices will be provided to those who do not have high-speed internet at home. All participants will receive a subsidy to offset the cost of increased home internet use for the duration of the study. To maximize participant engagement, the trial coordinator will provide weekly reminders for the duration of the program through SMS text messages or email, depending on the participant’s preference.

At each follow-up visit (Table 3), the study coordinator will review the interim medical history using a study case report form and have the participants complete the study questionnaires.

**Table 3 table3:** Schedule of activities.

Procedures	Baseline	8 weeks (±2 weeks)	3 months (±2 weeks)	6 months (±4 weeks)	12 months (±4 weeks)
Informed consent	✓				
Baseline demographics questionnaire	✓				
Problem Areas in Diabetes-Teen version (diabetes distress)	✓	✓	✓	✓	✓
Self-compassion Scale for Youth (self-compassion)	✓	✓	✓	✓	✓
Intervention satisfaction survey^a^		✓			
Patient Health Questionnaire (depression and suicidality)	✓	✓	✓	✓	✓
Generalized Anxiety 7-item scale (anxiety)	✓	✓	✓	✓	✓
Diabetes Eating Problem Survey-Revised version (eating disorders)	✓	✓	✓	✓	✓
Hemoglobin A_1C_	✓				✓
Time in range	✓	✓	✓	✓	✓
Review interval medical history	✓	✓	✓	✓	✓

^a^The intervention satisfaction survey will be given to the participants in the mindful self-compassion for teens (MSC-T) intervention group only.

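### The exploratory model of whether the effect on diabetes distress changes over time leaves out the 8-week PAID-T score, so it cannot see any change between programme end and 3 months.

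*Protocol article*

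**What the plan says.** Protocol article, Objectives: the first exploratory objective is to "explore if the effect of the MSC-T intervention changes over time throughout the 12-month follow-up period". Data and Outcome Measures describes the same aim as "exploring the interaction of time (ie, study time point) with DD" and excludes no visit.

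Trial Management, Table 3: PAID-T is scheduled at baseline, 8 weeks, 3, 6 and 12 months. Only the satisfaction survey is limited to the intervention arm, so 8-week PAID-T scores are due in both arms. The 8-week window is ±2 weeks.

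Intervention Group: the programme has 8 weekly sessions, and one fidelity check is "assessing the change in self-compassion between baseline and 8 weeks". The protocol thus itself uses 8 weeks as its before-and-after point.

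Analyses for Exploratory Outcomes: for DD over time, "we will use the 3-, 6-, and 12-month data to fit a linear mixed effects model". The listed terms are time, age, baseline DD, time by group and a random intercept. No reason is given for starting at 3 months. For time in range the text reads "Linear mixed effects models, adjusted for age, baseline time in range, and a random intercept", with no term for time, although this outcome is also collected at every visit.

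**The concern.** The objective spans the full follow-up, but the model that answers it starts at 3 months. The section does not merely leave the visits open for a later document. It lists them, and the list is shorter than both the schedule and the objective. For a time-limited course, the end of the course is a natural reference for asking whether benefit persists, fades or builds. That visit is the one left out.

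Two things are at stake. A change in effect between programme end and 3 months is invisible to the model. And anyone assessed at 8 weeks but at no later visit contributes nothing to it, in a trial that allows for 30% attrition.

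A smaller matter is the time-in-range model. Without a visit term, its group estimate can pick up a general trend over the year if the arms differ in which visits are missing.

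**Working it through.** **Visits.** Table 3 has four post-baseline PAID-T visits and the model uses three. Taking 3 months as about 13 weeks, the excluded interval is nominally 13 - 8 = 5 weeks. With the windows (weeks 6 to 10 and weeks 11 to 15) the two visits can be 1 to 9 weeks apart.

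The protocol gives no power figure for this analysis, so there is none to reproduce. The rest is illustration.

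**Power of the time-by-group test.** Inputs from Sample Size: SD 26, 70 per arm, 30% attrition (70 × 0.7 = 49 per arm). Assumptions of this check: visit treated as a category, complete data on n per arm, equal correlation ρ of 0.5 to 0.7 between visits, and the effect patterns below.

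With k visits, the Wald test has k - 1 degrees of freedom and noncentrality

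λ = n × SS / [2 × SD² × (1 - ρ)],

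where SS is the sum of squared deviations of the visit effects from their mean. With SD² = 676, the denominator is 676 at ρ = 0.5 and 405.6 at ρ = 0.7. The range in each row runs from n = 49, ρ = 0.5 to n = 70, ρ = 0.7.

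| Effect at 8 wk, 3, 6, 12 mo | SS, 3 visits | SS, 4 visits | Power, 3 visits | Power, 4 visits |
|---|---|---|---|---|
| -12, -6, -6, -6 | 0 | 27 | 5% | 19% to 41% |
| -4, -12, -12, -12 | 0 | 48 | 5% | 32% to 67% |
| -12, -9, -6, -3 | 18 | 45 | 16% to 33% | 30% to 64% |
| -12, -12, -12, -6 | 24 | 27 | 20% to 43% | 19% to 41% |

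Worked example, row 1 with four visits: the mean effect is -7.5 and SS = 4.5² + 3 × 1.5² = 27. At n = 49, ρ = 0.5, λ = 49 × 27 / 676 = 1.96, and power on 3 df is 19%. At n = 70, ρ = 0.7, λ = 70 × 27 / 405.6 = 4.66, and power is 41%. With the three planned visits the effects are equal, so SS = 0, λ = 0 and power equals alpha.

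In row 4 the effect changes only after 6 months. The extra visit then adds little to SS and costs one degree of freedom, so there is no gain.

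**Time in range.** A simulation used 70 per arm, no true group effect, a decline of 2 points per visit, a between-person SD of 12 and a within-person SD of 8, all assumed. It ran 150 replicates and fitted a random-intercept model with and without visit.

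- 20% missing in each arm after the first follow-up visit: the mean group estimate is 0.08 in both models, with SE 2.17 in both.
- 10% v 50% missing: the mean is 0.55 without visit and -0.17 with it, a shift of about 0.7 points. The simulation error of each mean is about 2.17/√150 = 0.18, so -0.17 is compatible with zero.

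**The case against.** A reader might infer that the trial cannot say whether benefit fades once the sessions end. The protocol does not support that. The 3-, 6- and 12-month visits nominally all fall after the last session, and the planned interaction tests fading across them. What is lost is the stretch from 8 weeks to 3 months.

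A reader might also infer that the 8-week scores are thrown away. They are not. Statistical Analysis summarises the mental health measures by group at each time point, and the visit also serves the fidelity check and the satisfaction survey. The missing-data section imputes outcomes for participants with at least one available data point, which could include someone seen only at 8 weeks. The loss is confined to this one model.

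Starting at 3 months matches the primary endpoint and may be deliberate, and the 8-week window opens at week 6, so it is not a clean end-of-programme measure. Both points are fair. But the protocol states no such reason, and an imprecise visit calls for care in reading it rather than for leaving it out.

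On time in range, the objective is a group comparison, not change in effect over time, and under equal missingness the visit term makes no difference. That reduces this part to a minor addition.

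The random intercept and the phrasing of the interaction in Data and Outcome Measures might also be read as errors. A random intercept is a standard choice and nothing here shows that it does harm. The phrasing is loose, but its sentence concerns the intervention effect on DD, so its meaning is clear.

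**Conclusion.** The point holds at low priority. The model for change in effect over time covers less than its objective and omits a visit that is scheduled in both arms. A change confined to the interval from 8 weeks to 3 months has only alpha-level (5%) power as planned. Including the visit gives 19% to 41% or 32% to 67% in the two early-change patterns and roughly doubles power for a steady fade. If the effect changes only late, the gain is small or nil.

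These powers depend on the assumed effect patterns, SD 26, equal correlations of 0.5 to 0.7 and 49 to 70 complete participants per arm. The protocol states neither the correlations nor the patterns. That the planned model has no information on the interval before 3 months depends on none of them.

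The missing visit term for time in range is minor and matters only if missingness differs by arm. Both analyses are exploratory, and the primary 3-month comparison and the secondary analyses are untouched.

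**What to change.** Fit the DD-over-time model to the 8-week, 3-, 6- and 12-month scores, with visit as a category, group and visit-by-group, keeping age and baseline DD. Report the group difference at each visit with its interval. Note beside the 8-week result that its ±2-week window may include assessments made before the last session. If there is a reason to start at 3 months, state it and narrow the objective to change in effect from 3 to 12 months.

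Add visit as a category to the time-in-range model. This protects the group estimate if missingness differs by arm and costs nothing if it does not.

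The cost is a few lines of analysis text. Both measures are already scheduled at every visit, so no further data collection is needed.
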